### Experimental Components

#### Goal Setting

Participants received a goal by text message each day they self-reported their steps. The static intervention groups received the standard 10,000 steps per day goal, with immediate or delayed reinforcement for goal attainment. Participants assigned to the adaptive goal group received performance-based goals based on an algorithm developed by the research team. This algorithm was adapted from recent developments in basic science around percentile schedules of reinforcement [18,29]. The preceding nine observations (typically last 9 days) of data were used to derive a rank-ordered percentile goal. The percentile algorithm requires (1) continuous and repeated measurements of PA, (2) ranking of a sample of behavior (steps/day) from lowest to highest, and (3) calculation of a new goal based on an *n*th percentile criterion.

To illustrate, if a participant’s step count for the preceding 9 days was 1000, 1500, 2600, 4500, 5000, 5700, 6300, 8000, 11,000, rank-ordered from lowest to highest, using a 60th percentile criteria, then 5700 steps becomes the participant’s next goal. The baseline phase provides data for the first goal and then a 9-day “moving window” adapts in each new day’s step count to calculate the next goal. The newest step count observation replaces the oldest step count observation. The 60th percentile was chosen based on previous PA research by Adams [16,20].

It is important to highlight that prescribed adaptive goals always fall within each participant’s recent abilities due to the moving window of the last 9 days. This is distinct from the static intervention group, which receives the commonly recommended goal of at least 8000-10,000 steps 5 days/week, which may be well beyond their current abilities. Because adaptive goals adjust daily, participants were informed that each new goal is good for only one day. We believe this encourages participants to send in step reports daily unprompted.

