#### Praise Messages

Several health behavior theories indicate that it is critical to praise improvements to develop new behavior or strengthen a habit [8,30,31]. The combination of goals and feedback was expected to provide a strong PA-shaping program. Delayed reinforcement participants did not receive contingent praise for achieving goals but did receive incentives on a monthly basis. Participants assigned to the immediate reinforcement groups received contingent differential feedback depending on whether a daily goal was met. Participants who did not meet the goal were provided a simple confirmation that steps were entered correctly and provided their next day’s goal (eg, “Steps Received. Goal for 4/1/14 is 4525 steps”). This approach avoids negative messages that could be discouraging. Each time a participant met a goal, a single message from the pool of praise messages was sent to the participant (eg, “Well done! You’re steps closer to good health. Goal for 4/1/14 is 4525”). Some messages used the participant’s first name for enhanced personalization.

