#### Reward Points and Incentives

Participants assigned to the delayed reinforcement groups received progressively increasing incentives each month for participating in the study (month 1=$5; months 2 and 3=$10 each; month 4=$20; total $45). Participants assigned to the immediate reinforcement groups received a point-based incentive each time they met a step goal. They had the opportunity to earn a point once per day (110 points possible) when a goal was met by the end of the day. Points were automatically exchanged for incentives ($5 for every 5 points earned) during the study. Participants self-selected their incentive from a list of retail options (eg, Amazon, iTunes, Target) or a charity (ie, the United Way), and all incentives were sent as electronic gift cards. To prevent habituation or satiation, they were allowed to change their choice at any time. Incentive amounts for delayed reinforcement groups approximate the total amount made available to the immediate reinforcement groups to control for cumulative amount of incentives.

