## Discussion

### Principal Considerations

This study integrates measures of behavior change and physiological outcomes to evaluate intervention strategies and mechanisms that improve health through adoption of walking behaviors over 4 months in an inactive, overweight/obese adult sample. The study examines the effects of two experimental factors: (1) percentile shaping to produce performance-based adaptive goals, versus typical static goals of 10,000 steps/day, and (2) reward structure using principles of behavioral economics (ie, US $1 per daily goal achieved, obtained immediately as goal achievement is reported), versus a delayed incentive. The group with a combination of static goals and delayed reinforcement approximates procedures found in practical settings (eg, a physician offering a PA brochure, recommending 10,000 steps/day, and giving a pedometer to a patient) with the difference being a predetermined monthly reward for continuing with the study—a common approach in many research studies [16,20,51,52].

Our factorial study design allows examination of the independent and joint effects of these components and explores the promise of percentile shaping and small immediate rewards to optimize behavioral interventions. Our work will contribute to the field by testing specific methodologies that link behavior change theory to practical applications. The limited body of research on shaping to improve PA shows complementary results, even with differing methodological approaches [16,19,20]. Further, employing mHealth strategies, such as SMS for treatment delivery and reward mechanisms, and wearable activity monitoring with feedback and wireless upload, enhance the overall treatment and theoretical fidelity [53] while capitalizing on the omnipresence of mobile technology.

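### The stated control for cumulative incentive fails on the article's own figures ($45 fixed versus up to $110), and Reinforcement x Phase compares two reward packages, not immediacy alone

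*Protocol article*

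**What the plan says.** The second factor is named immediate versus delayed reinforcement, and its rationale (Reinforcement Schedule: Immediate Versus Delayed) rests on how soon a reward follows the behaviour.

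- **Delayed groups, money.** Under Reward Points and Incentives they "received progressively increasing incentives each month for participating in the study", with the schedule "month 1=$5; months 2 and 3=$10 each; month 4=$20; total $45". Principal Considerations likewise describes this as a reward fixed in advance for staying in the study.
- **Immediate groups, money.** The same section says: "They had the opportunity to earn a point once per day (110 points possible) when a goal was met by the end of the day". The exchange rate into gift cards is $5 for every five points. Text Message System says the $5 is sent when the fifth point is earned.
- **Claimed control.** "Incentive amounts for delayed reinforcement groups approximate the total amount made available to the immediate reinforcement groups to control for cumulative amount of incentives".
- **Praise.** "Delayed reinforcement participants did not receive contingent praise for achieving goals" (Praise Messages). The immediate groups do receive it.
- **Two differing descriptions.** Goal Setting says the static groups had their goal "with immediate or delayed reinforcement for goal attainment". Principal Considerations describes the immediate reward as "US $1 per daily goal achieved, obtained immediately as goal achievement is reported".

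Data Analysis tests each component through its interaction with Phase and adds a Goal Type x Reinforcement Type x Phase term.

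**The concern.** Reinforcement x Phase is one of the two component effects in the primary aim. The sentence on incentive amounts tells the reader that total money has been removed as an explanation for any difference. If it has not, and if what is rewarded and whether praise follows also differ between the groups, then a difference in step change cannot be credited to the timing of reward. Conclusions about immediacy would go further than the contrast allows, and so would any use of them in later interventions.

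**Working it through.** **Step 1. Reproduce the stated total.** Delayed groups: 5 + 10 + 10 + 20 = $45. This agrees with the article.

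**Step 2. Amount available to the immediate groups.** 110 points x ($5 / 5 points) = $110. The rate of $1 per goal in Principal Considerations agrees. Difference: 110 - 45 = $65. Ratio: 110 / 45 = 2.44. The control sentence refers to the amount made available, so $110 is the figure to compare. It is a ceiling, reached only if every daily goal is met.

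**Step 3. Could expected earnings have been meant?** In points, equality needs 45 / 110 = 0.409, so about 41% of goals met. To obtain expected pay, let X be the number of goals met, assume X is Binomial(110, p), and pay 5 x floor(X / 5), because money is released only in $5 blocks:

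| Assumed share of goals met | Expected points | Expected payout | Ratio to $45 |
|---|---|---|---|
| 20% | 22 | $20 | 0.44 |
| 30% | 33 | $31 | 0.69 |
| 40% | 44 | $42 | 0.93 |
| 50% | 55 | $53 | 1.18 |
| 60% | 66 | $64 | 1.42 |
| 80% | 88 | $86 | 1.91 |
| 100% | 110 | $110 | 2.44 |

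The attainment rates are assumptions, since the article gives none.

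**Step 4. Adaptive groups with unchanged behaviour.** The goal is the 6th of nine ranked days. If the next day is exchangeable with those nine and ties are ignored, it exceeds the 6th with probability (9 + 1 - 6) / 10 = 0.40. That gives 44 points and about $42 paid, close to $45. The match lasts only while step counts stay stable, and the trial aims to raise them.

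**Step 5. Static groups.** Nothing ties attainment of 10,000 steps to 40%. Eligibility excludes only people reaching that level on five or more days a week, so baseline attainment can lie anywhere from none to 4/7. At the upper end, 110 x 4/7 = 62.9 points, or about $61 expected. With unchanged behaviour the range is therefore $0 to about $61.

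**Step 6. What else differs between the two levels.**

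| Feature | Immediate | Delayed |
|---|---|---|
| Money depends on | meeting the daily goal | participating |
| Praise for meeting the goal | yes | no |
| Money released | at each fifth point | monthly, fixed schedule |
| Total available | up to $110 | $45 |

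**Step 7. When the money arrives.** The point is credited at once, but the gift card follows the fifth point. At attainment p the mean wait for the first $5 is 5 / p days. At p = 0.40 this is 12.5 days.

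**The case against.** The strongest reply is that the package is disclosed. The Methods overview defines the immediate level as praise plus a point for each goal met and the delayed level as monthly incentives. The sections on praise and incentives spell out the rest. Randomisation makes the comparison of those packages valid, and allocation, outcome model and power are untouched. All of this stands. It leaves the control-of-amount sentence, which the figures contradict, and the attribution to immediacy.

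The sponsor may also say that expected earnings were meant. Step 4 shows this is plausible for an adaptive participant whose behaviour does not change. The article does not say so, and the argument does not carry over to the static groups.

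The phrase in Goal Setting may be loose wording, because the dedicated incentive text is explicit. The dollar described as obtained immediately may mean the credited point. Both readings are fair, and both call for reconciliation rather than a charge of error.

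Three stronger readings are tempting but not supported:

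- *That immediate participants were paid more, so a positive result may only reflect more money.* $110 is a maximum, and below about 41% attainment the immediate groups earn less than $45.
- *That static/immediate pay, or its delay, can be projected from the nine step counts in Goal Setting.* Those numbers only illustrate the percentile calculation and are not an attainment rate.
- *That reward density varying with Goal Type is a flaw.* It follows from how the goals are set and belongs to the combination that the three-way term tests.

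Nor did the delayed groups go without encouragement altogether. All groups received motivational prompts (Text Message Prompts). What the delayed groups lacked was praise contingent on meeting a goal.

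**Conclusion.** The point holds in this form. As worded, the control sentence is wrong: $45 fixed against up to $110, a 2.44-fold difference in what is available. Cumulative incentive is not controlled by design, because equality requires about 41% attainment, which is neither stated nor tied to the static goal. The direction of any realised difference in pay is unknown from the document. The expected payouts above rest on assumed attainment with independent days, but the comparison of available amounts needs no assumption.

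Contingency and contingent praise differ along with timing, so even equal dollars would not isolate immediacy. Reinforcement x Phase remains a valid randomised estimate of one reward package against another. The defect lies in interpretation and in a stated design property, not in the validity of the test.

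**What to change.** 1. Delete the control-of-amount sentence, or correct it to give the $110 maximum against the fixed $45. If expected earnings were intended, state that basis and the attainment rate assumed for each goal type.
2. Reconcile Goal Setting with Reward Points and Incentives and Principal Considerations on whether the delayed payment depends on goals. Reconcile Principal Considerations with Reward Points and Incentives and Text Message System on when money is released.
3. State that Reinforcement x Phase estimates goal-contingent praise and points, paid out per five goals met, against a fixed monthly participation payment without contingent praise. Word conclusions to match.
4. For each of the four cells, report realised dollars, share of days rewarded and time to first payment, beside the Reinforcement and Goal x Reinforcement results.

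The cost is a few sentences and one descriptive table. Text traffic is logged and the $5 incentives are sent automatically by the system, so no new data collection is needed. Data collection is complete but the main analyses are still to come, so the wording can be settled before results are interpreted.

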### Additional Intervention Components

#### Overview

All four groups received the following: (1) Fitbit Zip, (2) SMS based self-monitoring and reporting of steps per day, (3) brief health information, and (4) text message prompts. Random allocation was performed by a researcher who did not have contact with participants during screening or assessments and who knew them only by participant identification number.

#### Objectively Measured Physical Activity

Participants in all four groups received a commercially available accelerometer (Fitbit Zip, Fitbit Inc.) to wear for the 4-month duration of the study. Participants wore the accelerometer for at least 10 days prior to randomization to an intervention group and continued wearing for the remaining approximately 110 days. The Fitbit clips on clothing near the hip and has a small and unobtrusive form factor, thus accommodating various clothing styles to minimize non-wear. Participants were asked to wear the Fitbit during all waking hours (ie, at least 10 hours) every day for the duration of the study (ie, both the baseline and intervention phases), removing it for sleeping or in circumstances that might submerge it in water (eg, swimming). Fitbit accelerometers have excellent reliability and validity for measuring steps compared to direct observation and Actical accelerometers [32,33]. The Fitbit recorded steps and transmitted the data to the study team via the Internet to verify participants’ texted step reports. The accelerometer’s display was masked during baseline (to avoid participant reactivity) and then unmasked at randomization. Participants were also asked to sync their Fitbit each day using a personal computer connected to the Internet and the Fitbit sync dongle. Instructions on how to install the software were provided and demonstrated in the lab. The study team initiated and created study-managed accounts on the Fitbit website so participants were *not* able to access or view activity history, nutrition trackers, “badges” earned, social media interfaces, and other online tools that could have acted as potential confounders. To further limit access to the Fitbit website, we did not allow participants to sync their Fitbit using Fitbit’s mobile phone app because this required logging into the study-managed account. Fitbit, Inc. allowed researcher access to their Application Programming Interface (API) but otherwise was not involved with this project.

#### Text Message System

The study’s software engineer developed a proprietary automated text message system with the principal investigator. The texting system was the “front end” for participants to interact with the study and used a commercial SMS gateway service (Twilio) with a designated study SMS phone number. Participants in all four groups were instructed to send a “step report” text message to this number each night after 8 p.m. The “step report” is a daily step count in a specified format (eg, “5555 today”). The system was fully automated to recognize step reports, in a pre-determined set of natural language patterns, from all other types of messages. All SMS traffic was logged in a server database. Automated feedback was provided as per the participant’s intervention assignment when a step report was obtained. Participants in the immediate reinforcement groups received a US $5 incentive email automatically from the system upon meeting a daily goal when the 5^th^ point was earned.

Text messages were sent to all participants daily through this same study SMS number. Participants could text message “goal” at any time to receive an automated reminder of their step goal for that day. When a message was not recognized by the system (eg, “I lost my Fitbit”), it was immediately forwarded to the on-duty researcher’s mobile device with a prefix of the participant’s study identification number. The system facilitated researcher-initiated messages to participants through the system’s phone number (ie, all messages appeared to come from the SMS phone number regardless of the mobile device it originated from). Researchers could send texts to a specific participant or to all participants as group (see Figure 2 for a diagram of the system).

**Figure 2 figure2:**
[figure not shown]
Schematic for intensive adaptive intervention system.

#### Health Information Brochures

Upon randomization, participants in all four groups were sent two brochures on PA via email. A US Health and Human Services brochure [34] presents information on overcoming barriers to being active, initiating a PA routine, and recommendations on quantity of PA to evoke health benefits. An America on the Move Foundation brochure [35] suggests 100 ways to increase steps (eg, “take your dog for a walk”) throughout the day. Participants in all groups received the same materials on the first intervention day only.

#### Text Message Prompts

All participants in the intervention phase received daily text message prompts (≤160 characters) to encourage PA, except when Ecological Momentary Assessment (EMA) questions were administered (see Table 2). A randomly selected message (or EMA question) was sent at a random time of day between the hours of 8 a.m. and 6 p.m. local time. The research team developed a pool of messages that complemented or expanded on the health information brochures. The prompts included motivational quotes, health risks of inactivity, benefits of PA, and encouragement to be active (eg, “It doesn’t matter how old you are – it’s never too early or too late to become physically active so start today; only then will you start to see results!”). Acknowledging that maintaining participation over a 4-month study is often difficult, these unvalidated prompts were primarily a mechanism to remind participants of their involvement and served as somewhat of a disguise for the experimental components under manipulation (ie, the goal-setting and reinforcement types).

### Office Visits and Secondary Outcome Measures

Eligible participants visited the laboratory twice for about 2 hours each time. The initial visit included the written informed consent, physical activity PAR-Q+, the pre-measures as listed in Table 2, and training on the Fitbit and the texting system. At the second visit, the participant returned the Fitbit, completed post-measures (similar to pre-, except where noted in Table 2 [36-49]), and was debriefed regarding the study purpose. Data collection staff were blinded to treatment allocation at pre- and post-measures. However, it was impossible to blind participants as treatment groups were explained in the consent process.

**Table 2 table2:** Secondary outcome measures.

Measure		Description	Frequency		
			Pre-post	Once	Other
**Self-administered computerized surveys**					
	IPAQ long form	IPAQ long form; 31-item survey designed to capture details on domain-specific physical activity with acceptable test-retest (*r*=.8) and criterion validity (*r*=.3) [36] and intraclass correlation coefficient=.27-.71 [37].	x		
	Neighborhood	Neighborhood Environment Walkability Scale abbreviated; 54-item survey to measure neighborhood characteristics [38-40].		x^b^	
	Monetary choice	Delayed discounting protocol using 27-item self-administered questionnaire [41,42].		x^c^	
	Satisfaction	Consumer satisfaction style questionnaire for rating experience and providing feedback; question number and type differed by intervention assignment.		x^c^	
	Self-Efficacy	Single-item Ecological Momentary Assessment (EMA) of self-efficacy (0-9 Likert-type scale) delivered via SMS on 21 random intervention days. Item language based on previous work [43,44].			x
**Researcher performed laboratory measures**					
	Height and weight	Measured using digital stadiometer and scale (Seca 284 measuring station, Seca GmbH & co. KG).	x		
	Aerobic fitness	Aerobic capacity (VO_2peak_) estimated using a submaximal continuous treadmill ramp protocol (modified Balke) and the Foster equation [45-47].	x		
	Body composition^a^	Dual-energy x-ray absorptiometry (Lunar iDXA, GE Healthcare).	x		
	Blood pressure^a^	Brachial and central blood pressure assessed during pulse wave analysis using Sphymocor XCEL (AtCor Medical Inc) [48,49].	x		
	Arterial stiffness^a^	Carotid-femoral pulse wave velocity assessed using Sphymocor XCEL (AtCor Medical Inc) [48,49].	x		
	Biochemical^a^	Venous blood samples for cardiovascular risk and inflammatory markers; post-centrifugation samples archived in aliquots at -80°C.	x		

^a^Measured in the vascular subset of participants.

^b^Measured once at initial visit; second done at follow-up only if moved during study.

^c^Measured at follow-up visit only.

### Statistical Analysis

#### Power and Sample Size Determination

To estimate the sample size required to test the main aim of changes to steps/day, we conducted a set of simulations using a SAS macro developed by Psioda [50] and effect size estimates derived from findings reported by Adams et al [16]. Across the simulation runs, we varied the number of participants (Ns of 60-96), the magnitude of change from baseline to intervention Phase (1200 vs 1600 steps/day), magnitude of Goal Type (Static vs Adaptive) x Phase interaction effect (800 vs 1200 steps/day between-group difference in the magnitude of the Phase effect; compare to 1130 steps/day difference reported by Adams et al [16]), magnitude of Reinforcement Schedule (Delayed vs Immediate) x Phase interaction (300 vs 500 steps/day between-group difference in the magnitude of the Phase effect), and the Goal x Reinforcement x Phase interaction (150 vs 300 steps/day difference in Phase effect over and above the main effects and 2-way interaction effects). The simulations revealed that under the most conservative sets of assumptions (ie, sets comprising combinations of the smallest effect magnitudes) and an assumed attrition rate of 20%, a total initial sample size of N=100 participants (n=25 per group) would be required to have power of .80 or greater to detect hypothesized interaction effects.

